### Phase One RCT

A 1-week pilot RCT will determine the most effective and acceptable BFR-RT protocol in UK military patients, with the primary aim of reducing pain. This will be achieved by comparing two different BFR-RT pressures (high-pressure (80% LOP) vs low-pressure (40% LOP)) within a military residential rehabilitation setting. It is hypothesised that high-pressure BFR-RT will elicit a greater hypoalgesic response, but be less tolerable (ie, less total work completed with higher perception of effect).

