### Statistical methods and analysis

Descriptive data will be reported as the mean and SD for continuous variables and frequency statistics for non-continuous variables. Prior to statistical analysis, normality tests will establish data distribution; if data are non-normally distributed, transformation and the use of non-parametric statistical analysis tests will be employed. All tests will be two-sided, and alpha significant will be set a priori p<0.05. A between-subjects and within-subjects ANOVA will be used to assess the effect of the intervention on all outcome variables. Any statistically significant two-way interactions will be followed up using post hoc analysis with Bonferroni corrections to account for multiple comparisons. The magnitude of any differences will be presented using 95% CI and Cohen’s D for effect size.

Supporting analysis of the primary outcome will include a per-protocol analysis including patients with compliance >80% to intervention. In addition to the primary adjusted analysis, the unadjusted mean differences between groups will be reported using t-test, reporting 95% CI. Study participant flow will be recorded and reported as per CONSORT guidelines. Analysis will be conducted on a pairwise case basis. Therefore, all missing data will be reported, and patterns investigated. Sensitivity analysis will be conducted using multiple imputation techniques to assess the effect of missing data on primary outcomes. Post-intervention adverse events between groups will be analysed using Fisher’s exact test. All analysis will be conducted using SPSS.

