#### Patient-reported outcome measures

The PROMs used in Phase One (BPI, LEFS and injury-specific) will also be used within Phase Two, collected at T0_P2_, T3_P2_ and T4_P2_. Additionally, secondary outcome measures will be collected, including the Fatigue Assessment Scale, McGill Pain Questionnaire – Short Form, Pain Catastrophising Scale and Tampa Scale of Kinesiophobia. These secondary outcome measures will be collected at T0_P2_ and T4_P2_ only. The assessment of tolerability and daily response will again be monitored using the participant monitoring booklet (T2_P2_). The data collection schedule for all outcome measures can be found in online supplemental file 3.

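### The pairwise missing-data rule does not fit the repeated-measures ANOVA, so the primary pain analysis would in practice be complete-case

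*Protocol article*

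**What the plan says.** All of the following stands in the protocol article, mainly under Statistical methods and analysis.

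- Model: "A between-subjects and within-subjects ANOVA will be used to assess the effect of the intervention on all outcome variables".
- Missing-data rule: "Analysis will be conducted on a pairwise case basis". The text adds that missing data will be reported and their patterns investigated.
- Sensitivity: "Sensitivity analysis will be conducted using multiple imputation techniques to assess the effect of missing data on primary outcomes".
- Supporting analyses: "Supporting analysis of the primary outcome will include a per-protocol analysis including patients with compliance >80% to intervention", and unadjusted between-group differences by t-test.
- Software: "All analysis will be conducted using SPSS".

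The Sample size calculation section names three timepoints for Phase One and four for Phase Two. It requires 24 and 22 patients, allows 10% drop-out, and recruits 28 and 26. The Phase Two section on the experimental intervention chooses the pressure first by BPI, then by the Lower Extremity Function Scale (LEFS) if pain shows no statistically significant difference, and otherwise defaults to low pressure.

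**The concern.** Pairwise deletion means that each comparison of two variables, or of two visits, uses every patient who has both values. That is workable for a correlation, a t-test or a two-visit contrast. The omnibus repeated-measures ANOVA works differently: it needs a full row of visits for each patient and removes any patient with a gap. A reader of the pairwise sentence would expect partly observed patients to contribute to the main result, but under the named model they would not.

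Two things are at stake.

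- **Discarded data.** A patient with two of three BPI forms contributes nothing to the primary test, in trials of 28 and 26 patients. The t-tests could then rest on a different set of patients from the ANOVA.
- **Possible bias.** If missing BPI values were related to pain and more common in one arm, deleting those patients would make that arm's pain look lower. In Phase One this is the comparison that selects the Phase Two pressure. The per-protocol analysis would not correct this, because it also restricts the set of patients.

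**Working it through.** **1. Can any reading of the rule fit the model?**

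| Reading of pairwise | t-tests and two-visit contrasts | Omnibus ANOVA |
|---|---|---|
| Each pair of visits uses the patients who have both | possible | not possible; a full row is needed |
| Exclusion decided separately for each analysis | possible | every incomplete patient still drops out |

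On either reading the primary ANOVA is complete-case.

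**2. The plan's sample sizes.** Inputs from the Sample size calculation section: effect size 0.64, power 0.95, alpha 0.05, two arms, m = 3 or 4 timepoints. The correlation between visits is not given; ρ = 0.5 is assumed. For the between-factors test, λ = f²·N·m / (1 + (m − 1)ρ), with 1 and N − 2 degrees of freedom.

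- Phase One: λ = 0.64² × 24 × 3 / (1 + 2 × 0.5) = 29.49 / 2 = 14.75; power 0.956.
- Phase Two: λ = 0.64² × 22 × 4 / (1 + 3 × 0.5) = 36.04 / 2.5 = 14.42; power 0.951.
- Drop-out: 24 / 0.9 = 26.7, so 27, and 28 as an even total; 22 / 0.9 = 24.4, so 25, and 26 as an even total.

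The stated figures reproduce when 0.64 is entered as Cohen's f. The plan labels it d; that is a separate matter, but the power figures below rest on it.

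**3. Complete patients if forms are missing independently.** The documents give no missing rate per visit, so the rate q is an assumption. Expected complete patients = N(1 − q)^m. Power uses f = 0.64 and ρ = 0.5, with the count rounded down to an even number.

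| q per visit | Phase One (28, 3 visits; 24 required) | Power | Phase Two (26, 4 visits; 22 required) | Power |
|---|---|---|---|---|
| 3% | 25.6 | 0.96 | 23.0 | 0.95 |
| 5% | 24.0 | 0.96 | 21.2 | 0.93 |
| 10% | 20.4 | 0.91 | 17.1 | 0.85 |

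For example, 28 × 0.95³ = 24.0 and 26 × 0.95⁴ = 21.2.

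**4. Complete patients if the plan's own allowance holds.** If 10% of patients are incomplete in total, 28 × 0.9 = 25.2 and 26 × 0.9 = 23.4 remain. With 25 and 23 patients, power is 0.963 and 0.959.

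**5. Size of a possible bias.** This is an illustration by simulation under assumed conditions: SD 2, ρ = 0.5, three visits, no true difference between arms, deletion in one arm only, and log-odds of deletion rising by 1 per point of pain at the middle visit.

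| Share of that arm deleted | Shift in its mean at visits 1, 2, 3 | Average shift |
|---|---|---|
| 10% | −0.14, −0.28, −0.14 | −0.19 |
| 20% | −0.26, −0.52, −0.26 | −0.35 |
| 30% | −0.38, −0.75, −0.37 | −0.50 |

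The protocol gives 2 points as the minimally clinically important difference on the BPI. The table shows shifts in level. For change from baseline at 10%, the shift is −0.28 + 0.14 = −0.14 at the middle visit and about 0 at the last.

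**The case against.** The strongest reply is that this is a matter of wording with safeguards in place. Missing data will be reported, their patterns examined, and multiple imputation run on the primary outcome. Pairwise may simply mean analysis by analysis, which suits the t-tests and post hoc contrasts, and the estimation method could be left to an analysis plan that is not shown. Part of this stands: the safeguards are real, and the point would be weak if the article were only silent. But the article fixes both a model and a rule that the model cannot follow, and the imputation leaves the headline result unchanged.

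Four stronger readings are tempting, and the documents do not support them.

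- **High pressure will cause more missing pain data.** The hypothesis is that "high-pressure BFR-RT will elicit a greater hypoalgesic response, but be less tolerable", but the same sentence explains this as less work done and greater perceived effort, not as withdrawal or unreturned forms. Patients are on a 3-week residential course and the last Phase One assessment is on day 6, so someone who stops the restricted exercise may still complete a BPI. The article does not say whether collection continues after stopping.
- **Numbers will fall below 24 and 22.** That depends on the assumed rate. At 5% per visit Phase One keeps 24, and within the 10% allowance both phases stay above target. Independent gaps also cost more patients than clustered ones: a patient who leaves and misses several visits is lost only once.
- **Phase Two would lose patients over seven assessment dates.** The questionnaires "will also be used within Phase Two, collected at T0_P2_, T3_P2_ and T4_P2", which gives days −3, 1, 5, 6, 10, 11 and 15. The sample size section names four timepoints, and nothing says that the primary model uses all seven.
- **SPSS is the obstacle.** The article names SPSS but no procedure, and SPSS also fits mixed models. The limit lies in the conventional ANOVA.

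**Conclusion.** The point holds as a conflict of method. The stated handling cannot apply to the stated model, and the primary BPI analysis would in practice be complete-case, with multiple imputation only as sensitivity. This does not depend on any assumed rate.

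The consequences are conditional. Within the plan's 10% allowance the loss of power is negligible. At an assumed 5% of forms missing independently per visit, Phase One just meets its target and Phase Two falls about one patient short. Bias in the choice of pressure requires missingness that both relates to pain and differs by arm; the documents do not predict it. Under deliberately unfavourable assumptions the shift is about 0.2 points at 10% deletion, against a 2-point important difference. To decide the first step of the pressure choice, bias would also have to turn a non-significant BPI difference into a significant one. The case for change is that a better-suited method costs almost nothing, not that serious distortion has been shown.

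**What to change.** Delete the pairwise sentence. State that the primary analysis is a likelihood-based linear mixed model for repeated measures (SPSS MIXED, REML) on all randomised patients as randomised, using every available BPI value at the timepoints named in the Sample size calculation section: three in Phase One and four in Phase Two.

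Keep multiple imputation as the sensitivity analysis. A delta-adjusted version, which makes the imputed pain of patients with missing values worse by stated amounts, is optional. It is worth considering because the mixed model assumes data are missing at random and would not by itself cure missingness driven by unobserved pain.

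The cost is a change of wording in the analysis section, with no new data, patients or software.

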### Data management

All data will be completed on hard copy by participants and collected by the research team. Participants will be identified through a unique identification key. Data access will be restricted to pre-identified researchers to ensure confidentiality. Only the research team involved in data analysis will have data access rights. All data collected will be stored securely at the study site. All data used in this project are crown copyright protected. On completion of the study, raw and processed data underpinning publications will be archived and stored securely on the electronic data archiving system at the Academic Department of Military Rehabilitation within the Ministry of Defence. Data will be retained for 10 years. This trial is embedded within an existing clinical care pathway, and as it is not testing new pharmaceutical products or drugs; therefore, a formal data monitoring committee was not required. However, a study steering group (LG, LH and PL) will meet periodically to discuss matters arising related to adherence and data management.

### Adverse events

All clinical and research staff will be briefed, detailing the procedures for identifying and reporting adverse events. Information on any unexpected adverse events deemed to be related to study participation will be collected and reported to the chief investigator within 24 hours of its occurrence. A standardised proforma will be completed by the study site clinician which will detail the time and date of the incident, severity of the event, the relationship to the study and the action taken and overall outcome. All serious adverse events will be recorded and discussed directly with the MODREC. Reporting of safety incidents will be duplicated using existing clinical health and safety reporting procedures and in accordance with the principles of good clinical practice. It is not anticipated that there will be any risk to study participants.

## Methods and analysis: Phase One

### Study design

Phase One is a 1-week, single-centre, pilot RCT embedded within DMRC, Stanford Hall’s residential rehabilitation courses, running from October 2024 to August 2025. Injured serving military personnel will be randomly assigned to one of the following groups: (1) low-load resistance training with high-pressure BFR (BFR80) or (2) low-load resistance training with low-pressure BFR (BFR40). Both treatment arms will be delivered during week 1 of the participant’s 3-week residential rehabilitation course. The study design is outlined in figure 1.

**Figure 1 F1:**
[figure not shown]
Study design flow diagram: Phase One. Phase One timepoints—T0_P1_, baseline (day −3); T1_P1_, admission day (day 1); T2_P1_, daily (days 1–5); T3_P1_, end of intervention (day 5); T4_P1_, follow-up (day 6). BFR40, blood flow restriction with resistance training at 40% limb occlusion pressure; BFR80, blood flow restriction with resistance training at 80% limb occlusion pressure; DMRC, Defence Medical Rehabilitation Centre.

### Experimental intervention

During the first week of the residential rehabilitation course, participants in both groups will replace standardised knee dominant exercise with low-load BFR-RT at either low (ie, 40% LOP) or high (ie, 80% LOP) pressure, with previous literature reporting significant hypoalgesia following BFR exercise at both high and low pressures.^43 44^ Both experimental groups will complete seven BFR-RT sessions over the first week of the residential rehabilitation course (Monday–Friday). Using the Personalised Tourniquet System for BFR (Delfi Medical Innovations Inc, Vancouver BC, Canada), with an Easi-Fit BFR Cuff (single-bladder, contoured) fully encircling the limb and matching limb protection sleeve (24″×4.5″ or 34″×4.5″, dependent on limb size), each session will consist of a unilateral leg press exercise (Technogym, Bracknell, UK), followed by unilateral knee extension exercise with ankle weights (Komodo Sports, Huntingdon, UK), on the affected limb. The Personalised Tourniquet System for BFR automatically measures the individual’s LOP while at rest in supine (20–350 mm Hg±6 mm Hg of a set-point, 10 s average under non-transient conditions), which literature reports as a valid and reliable measure;^57^,^59^ thereafter, either 80% LOP (BFR80) or 40% LOP (BFR40) will be used based on the participants’ assigned group. Participants will complete 1 set of 30 repetitions, followed by 3 sets of 15 repetitions at 20% 1RM, with 30 s rest between sets (continuous inflation during exercise) and a 3 min reperfusion period between exercises. Both exercises will be performed using a 1:0:1 tempo (1 s concentric phase, no pause and 1 s eccentric phase). On the Wednesday and Thursday of the intervention week, BFR-RT will be performed twice daily, with sessions separated by >4 hours.

### Outcome measures

A full list of outcome measures and their respective data collection timepoints are provided in online supplemental file 3, with an overview of each patient-reported outcome measure (PROM) provided in online supplemental file 4. A description of each timepoint (T0_P1_ to T4_P1_) is provided in figure 2.

**Figure 2 F2:**
[figure not shown]
Timepoints of data collection for Phase One RCT (top) and Phase Two RCT (bottom). Phase One timepoints—T0_P1_, baseline (day −3); T1_P1_, admission day (day 1); T2_P1_, daily (days 1–5); T3_P1_, end of intervention (day 5); T4_P1_, follow-up (day 6). Phase Two timepoints—T0_P2_, baseline (day −3); T1_P2_, admission day (day 1); T2_P2_, daily (days 1–5, 6–10, 11–15); T3_P2_, start and end of residential rehabilitation weeks (days 1 and 5, 6 and 10, and 11 and 15); T4_P2_, end of intervention (day 15). BFR, blood flow restriction; BFR40, blood flow restriction with resistance training at 40% limb occlusion pressure; BFR80, blood flow restriction with resistance training at 80% limb occlusion pressure; RCT, randomised controlled trials.

#### Baseline characteristics

During Phase One, baseline data collection (T0_P1_) will include a participant demographics questionnaire, Health Anxiety Depression Scale,^60^ Musculoskeletal Health Questionnaire^61^ and medication history. Personal and demographic characteristics including age, body height, body mass, body mass index, duration of symptoms, previous injuries, previous treatment, military occupation, duration of military service, smoking and drinking habits will also be collected at T0_P1_.

#### Patient-reported outcome measures

The primary outcome measure of intervention efficacy will be the BPI;^62^ additionally, all participants will be asked to complete the Lower Extremity Function Scale (LEFS).^63^ A detailed description of all PROMs can be found in online supplemental file 4. All other PROMs listed will only be completed based on injury-specific site location. For example, an individual with a foot/ankle injury will only be asked to complete foot/ankle questionnaires, not knee or hip-specific questionnaires.

The BPI is a patient-administered, multidimensional, pain assessment tool commonly used within musculoskeletal clinical practice.^62^ Higher scores on the nine-item short form indicate greater interference with function, or greater pain intensity.^62^ Literature suggests the BPI has excellent test-retest reliability (intra-class correlation coefficient=0.90–0.96) and excellent internal consistency (Cronbach’s α=0.86–0.96) in populations with persistent neuropathic, nociceptive and nociplastic pain.^64^,^66^ The minimally clinically important difference for the BPI is a 2-point reduction for average pain, pain interference and pain severity.^67^,^69^

To assess the feasibility and tolerability of the BFR-RT interventions, a participant monitoring booklet will be used throughout the intervention period (T2_P1_). The booklet consists of multidimensional daily morning well-being questions, training load monitoring (sets × reps × load completed), sessional ratings of perceived exertion, and Numerical Pain Rating Scale (NPRS) for injury-specific pain and localised muscle soreness (NPRS; pre-intervention, immediately post-intervention and 1-hour post-intervention for each BFR-RT session).

#### Pressure pain threshold testing

Pressure pain threshold (PPT) testing is reported as the minimum pressure applied to cause pain and used to quantify pain sensitivity in persistent pain populations.^70^ It is suggested that PPT could be used as an indicator of persistent pain, as a reduction is consistent with hyperexcitability in central nervous system processing.^71^ The inter-rater and intra-rater reliability of PPT has previously been established as good to excellent, despite significant variation between measurement procedures being reported within the literature.^72^,^75^ For the collection of data within this pilot RCT, a member of research staff skilled in using a handheld pressure algometer (1 cm^2^ probe, Wagner Instruments, Greenwich, USA) will apply pressure at a rate of 1 kgf/s until the first point of perceived pain, whereby the participant will say ‘pain’ to indicate the perceived pain. The selected locations of measurement are based on existing literature:^43 44^

Bilateral quadriceps—test location measured 20 cm proximal to base of patella.Dominant biceps brachii—test location measured 10 cm proximal to the cubital fossa.Medial gastrocnemius of the injured/dominant limb—test location measured at 60% length of gastrocnemius muscle, measuring from calcaneus to popliteal fossa.Nondominant upper trapezius—test location measured at 10 cm from the acromion in direct line with the neck.Tibialis anterior of injured/dominant limb—test location measured at one-quarter of the distance between the superior edge of the fibular head and the most lateral part of the lateral malleolus was marked using a delible pen; then, half the distance from the palpated anterior-lateral edge of the tibia horizontal to the first mark is marked with a delible pen as testing location.

Pressure pain threshold testing will be completed at T0_P1_, T1_P1_, T2_P1_, T3_P1_ and T4_P1_. At each location, two measures will be collected, separated by 20 s, with the mean score for analysis (PPT quantified as the kilogram force applied at the point of ‘pain’). Thereafter, PPT testing will be completed pre-intervention, immediately post-intervention and 60 min post-intervention to assess the immediate and lasting effects of the intervention. Additionally, the pre-intervention PPT metrics on the following day will act as a 24-hour mechanistic measure of BFR-induced hypoalgesia following BFR intervention. As a result of assessing six separate points, we will be able to determine if the BFR interventions produce a systemic as well as a local hypoalgesic effect.

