
A scarcity of literature is currently available concerning the impact of the applied pressure (ie, LOP) and BFR-induced hypoalgesia effect. The acceptability and tolerance of higher relative BFR pressures in persistent pain populations are also unknown due to the complexity of presentation (eg, hyperalgesia) and the perception of discomfort experienced during BFR exercise.^47 48^ Research currently suggests that greater pressures (ie, 80% LOP) elicit a greater hypoalgesic response in response to a noxious stimulus in pain-free individuals;^43 44^ however, if greater pressures are not tolerated, the opportunity to promote hypoalgesia could be lost, and it is currently unknown whether higher pressures elicit a greater acute hypoalgesic response in individuals with pain/persistent pain. Additionally, lower relative pressures (ie, 40% LOP) have elicited a statistically significant hypoalgesic response in pain-free individuals,^43 44^ which therefore may be more clinically acceptable and tolerated within persistent pain populations. Within UK Defence Rehabilitation residential rehabilitation courses, physiotherapists and exercise rehabilitation instructors only get a limited period per day with injured personnel; therefore, leveraging short-term pain reduction from BFR-RT may allow additional exercise rehabilitation activities to occur, akin to the work by Hughes *et al*,^33^ Korakakis *et al*^49^ and Ladlow *et al*.^21^ The clinical and mechanistic (biomechanical and neuromuscular) underpinnings of high-frequency BFR-RT in UK military personnel with persistent knee pain are currently being investigated at multiple regional rehabilitation units.^50^ However, this study does not directly measure mechanisms of pain modulation.

Any intervention that can accelerate the progression of complex MSKI rehabilitation and ameliorate pain, while exercising at a lower relative training intensity, is of interest to UK Defence Rehabilitation services.^50^ Research investigating the efficacy and acceptability of different BFR training interventions during the rehabilitation of military personnel with lower limb MSKI primarily limited by pain is warranted. To develop our understanding of BFR-induced hypoalgesia and develop best practice guidelines, a pragmatic research study, embedded within a ‘real-world’ clinical setting, is proposed.

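### Phase One has no arm without BFR, so its pressure pain threshold readings can compare 80% with 40% LOP but cannot determine whether BFR produces local and systemic hypoalgesia

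*Protocol article*

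**What the plan says.** Under Pressure pain threshold testing (Phase One), the article plans PPT at six sites before, immediately after and 60 minutes after the intervention. It concludes that "we will be able to determine if the BFR interventions produce a systemic as well as a local hypoalgesic effect". The same paragraph presents the next day's pre-session reading as a 24-hour mechanistic measure of BFR-induced hypoalgesia.

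The Phase One Study design has two arms, BFR80 and BFR40. Under Experimental intervention, "Both experimental groups will complete seven BFR-RT sessions over the first week of the residential rehabilitation course", with the same sets, repetitions, load and exercises in each. The choice of pressures rests on "previous literature reporting significant hypoalgesia following BFR exercise at both high and low pressures". The Background adds that "lower relative pressures (ie, 40% LOP) have elicited a statistically significant hypoalgesic response in pain-free individuals". Study setting and Table 1 place both arms alongside a rehabilitation course in which several components list pain reduction among their aims.

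Statistical methods and analysis gives one general model: "A between-subjects and within-subjects ANOVA will be used to assess the effect of the intervention on all outcome variables". Methodological considerations and study limitations acknowledges the lack of an exercise-based control for Phase Two and does not mention Phase One.

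**The concern.** The sentence on six sites is a causal claim about BFR as such. To support it, Phase One would need participants who do not receive BFR, and it has none. Measuring more sites shows where PPT changes, not why. A general effect of exercise, of repeated algometry or of the course could also move remote sites, and would then look like a systemic effect of BFR.

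A better understanding of BFR-induced hypoalgesia is one of the reasons the Background gives for the study. As worded, the article invites a mechanistic conclusion from Phase One that its design cannot deliver. It also leaves room for the opposite mistake, in which similar arms are read as evidence that BFR does nothing.

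**Working it through.** **Inputs from the article.** Two arms, 1:1; 24 patients required and 28 recruited (14 per arm); two-sided alpha 0.05; PPT before, immediately after and 60 minutes after a session; a between- and within-subjects ANOVA. The article gives no SD, correlation or expected change for PPT, so those values are assumed below.

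**The plan's own figure.** The 24 patients are reproduced for a repeated measures ANOVA (between factors) with three timepoints and correlation 0.5, if 0.64 is entered as Cohen's f: noncentrality = N × f² × m / (1 + (m − 1) × rho) = 24 × 0.4096 × 3 / 2 = 14.75, df 1 and 22, power 0.956. Then 24 / 0.9 = 26.7, so 27, or 28 for equal arms. (The article labels 0.64 as d; that is a separate matter.) The calculation concerns the BPI; here 24 and 28 serve only as patient numbers.

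**What each ANOVA term estimates.** At a given site, let C be the mean PPT change from everything other than BFR (exercise, retest, course). Let B80 and B40 be what BFR adds at each assigned pressure.

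- Mean change in BFR80: C + B80
- Mean change in BFR40: C + B40
- Time term: C + (B80 + B40) / 2
- Group-by-time term: B80 − B40

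The claim concerns B80 and B40 themselves. Two observed means cannot separate three unknowns. The time term can be non-zero when B80 = B40 = 0, and the group-by-time term is zero both when BFR does nothing and when it works equally at both pressures. Each site adds two means and three more unknowns, so six sites do not solve this.

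**Illustration 1: paired test standing in for the time term, no BFR effect.** Noncentral t with noncentrality = shift × √N and N − 1 df. The shift is in SDs of the paired change and is assumed.

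| Assumed non-BFR shift | N = 24 | N = 28 |
|---|---|---|
| 0.2 | 0.2 × 4.90 = 0.98; rejects 16% | 0.2 × 5.29 = 1.06; rejects 18% |
| 0.3 | 1.47; 29% | 1.59; 33% |
| 0.5 | 2.45; 65% | 2.65; 72% |

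**Illustration 2: simulated 2 (group) × 3 (reading) mixed ANOVA, 28 patients, 4,000 runs per scenario.** Shifts are in SDs of a single reading and apply to both post-session readings. The three figures in a cell are for assumed correlations between readings of 0.5, 0.7 and 0.9.

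| Scenario | Time term rejects | Group-by-time rejects |
|---|---|---|
| No BFR effect, other causes +0.3 | 34 / 54 / 96% | about 5% |
| No BFR effect, other causes +0.5 | 76 / 95 / 100% | about 5% |
| BFR +0.5 in both arms, no other cause | 76 / 93 / 100% | about 5% |
| BFR +0.5 in both arms, other causes −0.5 | about 5% | about 5% |
| BFR 0 at 40%, +0.5 at 80% | 24 / 39 / 85% | 25 / 38 / 86% |

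Rows two and three describe opposite truths and give practically the same results. Row four hides a real BFR effect completely. Only in row five, where the pressures differ, does the group-by-time term move away from 5%.

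**The case against.** Several points on the other side have force.

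- **The pressure contrast is causal evidence.** The arms share one exercise prescription and differ by randomised pressure, and the stated hypothesis is that 80% LOP gives the greater hypoalgesia. A difference at local and remote sites would be randomised evidence of a local and systemic effect of assigned pressure. This stands. A reader might infer that Phase One PPT data say nothing about mechanism; that goes too far. What cannot be learned is BFR against no BFR, and what equal arms mean.
- **Remote sites act as an internal control.** Exercise and cuff are on the affected limb only, while PPT is also taken at the other quadriceps, the biceps and the trapezius. A treated-minus-remote contrast removes drift common to all sites. It does not remove local effects of the exercise itself, and it cannot support a claim about a systemic effect.
- **Earlier studies had a no-BFR condition.** The Background cites greater hypoalgesia with high-pressure BFR than with low-intensity exercise alone. It attributes this to pain-free participants, and says that the response to exercise in persistent pain is inconsistent and sometimes hyperalgesic. It cannot stand in for a comparator here.
- **The plan does not say it will read the time effect this way.** A reader might infer that a significant time effect will be reported as BFR hypoalgesia. The analysis section specifies follow-up only for significant two-way interactions and gives no rule for a time main effect. The fault is in the stated claim, not in a planned report.
- **The term may mean the whole BFR-RT package.** This does not help, because no Phase One arm goes without the package.

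**Conclusion.** The point holds as a limited correction. The statement that Phase One will determine whether BFR produces local and systemic hypoalgesia, and the label BFR-induced for the next-day reading, are not supported by a design in which both arms receive BFR. This follows from the design and rests on no assumed number. The rejection rates of 16% to 72% are illustrations under assumed shifts, not estimates for this trial.

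Two stronger readings should be resisted. A reader might infer that six sites make the claim easy to reach by chance alone; but the claim is a joint one, a rise at local and at remote sites, and one significant result at any site would not meet it. A reader might also infer that Phase Two settles the question. Its control arm receives standard rehabilitation, so the BFR-minus-control difference removes retest and course effects but cannot separate BFR from low-load exercise or from the replacement of the knee-dominant exercises.

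The consequence is modest. PPT is secondary, the sample size rests on the BPI, and the pressure for Phase Two is chosen on the BPI, then the LEFS, then a low-pressure default.

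**What to change.** 1. In Pressure pain threshold testing (Phase One), limit the conclusion to the randomised difference between 80% and 40% LOP in PPT change, with its 95% CI, from one model with site as a factor (local against remote, with each of the six sites classified in advance). Possible wording: Assessing six sites will allow us to estimate, at local and at remote sites, the difference in PPT change between the two pressures; changes over time within each arm will be described and not attributed to BFR.
2. In the same paragraph, drop the attribution BFR-induced for the next-day reading and call it a 24-hour post-session measure.
3. In Methodological considerations and study limitations, extend the statement on the missing control to Phase One: no arm goes without BFR, so similar arms fit both no effect and an equal effect.
4. In Pressure pain threshold (Phase Two), state that the BFR-minus-control difference in PPT change from baseline at the shared timepoints, with an arm-by-site term, estimates the local and remote effect of adding BFR-RT to the course in place of the knee-dominant exercises, and not the effect of BFR apart from low-load exercise.

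The cost is wording in these sections and one model specification, with no added patients, visits or measurements. The downside is that Phase One can no longer claim a BFR-specific mechanism.
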